#### Patient-level analysis

All analysis will be based on the intention-to-treat principle, including all recruited patients from within randomised wards. The total PEECH score will be analysed using a linear mixed-effect model with fixed effect being the intervention and the random effect will be ward in order to account for the potential of dependence of patient-level responses from patients within the same ward. The four subscales will be analysed using the same model. These models will allow the estimation of the parameters required for the planning of future trials, including the patient-level variation and between-ward variation. As with the HCA-level analysis, for the patient-level outcomes we will compare results from the random-effect model with those from a GEE model. The sensitivity of the assumption of a normally distributed outcome will be assessed using the two-stage non-parametric bootstrap.

If appropriate, sensitivity of the results to missing data will be checked via multiple imputation. If appropriate, adjustment for baseline factors will be made.

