### Recruitment

#### Wards

The ward manager provides permission for ward participation. Recruitment of wards will cease once permission is given by ward managers of 4 eligible wards from each of 3 acute NHS Hospital Trusts (*n* = 12 wards in total).

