### Allocation for trial interventions

Stratified by NHS Hospital Trust, 12 wards will be randomly allocated by the Norwich Clinical Trials Unit. Each ward has an equal chance of receiving either training for HCAs in relational care or training as usual. Random allocation is generated via computer-written code. To conceal allocation from those responsible for recruitment, randomisation takes place immediately after baseline measures are completed and 4 weeks ahead of the start of the intervention (set-up period) to allow appropriate arrangements including HCA cover.

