### Intervention

#### HCA training in relational care: Older People’s Shoes

HCAs from wards randomised to the new training intervention (*n* = 6 wards, 2 wards per hospital) will receive ‘Older People’s Shoes’, a newly developed HCA training package that focuses on the relational care of older people. The training intervention was developed using evidence from interviews with HCAs, other ward staff, older people, and a panel of experts. The intervention development work was funded by the same grant but in an earlier phase of this project. Course materials comprise a trainer manual and trainee workbook, PowerPoint resources and an online version of the training.

Training will take place during weeks 5 to 8 post-randomisation after the 4-week set-up period. It comprises 2 training days approximately 1 week apart. Older People’s Shoes training is delivered by registered nurses, all of whom are employed at the local Hospital Trust in practice development or education and training roles. These trainers receive full training in the content and delivery of ‘Older People’s Shoes’ from members of the research team.

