### Training as usual

HCAs from wards not randomised to the training intervention (*n* = 6 wards, 2 wards per Trust) will receive ‘training as usual’. This is typically restricted to periods of staff induction or focussed on mandatory training requirements such as manual handling. HCAs will receive no training in relational care beyond any that might be experienced as part of the standard process within their employing NHS Hospital Trust. Educational leads for each NHS Hospital Trust have provided details of how this is operationalised for HCAs within their organisation.

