#### Ward-level analysis

QUIS will be analysed as a total mean rating for each observed session. Analysis will be based on the change from baseline to outcome using a general linear model including NHS Hospital Trust as this was a stratification variable. Due to the small number of wards this analysis will be descriptive.

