#### HCA-level analysis

The outcomes of TEQ and AGED will be assessed using a linear mixed-effect model, with fixed effect being the intervention and the random effect will be ward. This will account for the potential of dependence of HCA-level responses from HCAs within the same ward. Additionally, the baseline value of the outcome will also be included as a fixed effect in a sensitivity analysis. These models will allow the estimation of the parameters required, including the within-ward and between-ward variance, for the planning of future trials, including the HCA-level variation and between-ward variation.

Due to the small number of clusters, the results of the random-effect model will also be compared to those using a generalised estimating equation (GEE) model. Additionally, as the number of clusters is less than 15 per arm [39], sensitivity will be analysed as a total average, per ward, rating as well as the individual sub-types. Due to the small number of wards involved this analysis will be descriptive. Additionally, the sensitivity of the assumption of a normally distributed outcome will be assessed using the two-stage, non-parametric bootstrap.

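### The PEECH, TEQ and AGED models omit NHS Trust, the stratification factor; if Trusts differ, the ward ICC is inflated for a Trust-stratified trial and intervals are conservative

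*Protocol article*

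**What the plan says.** Under Allocation for trial interventions, the protocol article states: "Stratified by NHS Hospital Trust, 12 wards will be randomly allocated". The Recruitment section takes "4 eligible wards from each of 3 acute NHS Hospital Trusts". The two arm descriptions give "2 wards per hospital" for the intervention and "2 wards per Trust" for training as usual, so allocation is 2:2 within each Trust.

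The three analysis sections treat this differently:

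- **Ward-level analysis (QUIS):** change from baseline is analysed "using a general linear model including NHS Hospital Trust as this was a stratification variable".
- **HCA-level analysis (TEQ, AGED):** a "linear mixed-effect model, with fixed effect being the intervention and the random effect will be ward". The sensitivity model adds only the baseline value of the outcome.
- **Patient-level analysis (PEECH, the primary outcome):** "The total PEECH score will be analysed using a linear mixed-effect model with fixed effect being the intervention and the random effect will be ward". The four subscales use the same model. A closing sentence allows covariate adjustment where judged suitable, without naming Trust.

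The opening of the Statistical analysis section says that the aim is to obtain sample-size parameters and confidence intervals rather than tests. The HCA and patient sections say that their models are to supply the between-ward variance for future planning.

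**The concern.** The reason given for putting Trust into the QUIS model applies equally to the other two levels, because the same 12 wards were randomised in the same strata. The HCA and patient sections write out their fixed and random effects, and Trust is in neither. This is an inconsistency between stated models, not a detail left to an analysis plan.

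Each Trust contributes two wards to each arm, so Trust differences cancel from the arm comparison. A model with only intervention and ward does not know this and counts most of any Trust difference as ward-to-ward variation. Two of the pilot's intended outputs are then affected: the between-ward variance (and ICC) passed on to a definitive trial, and the width of the confidence intervals.

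**Working it through.** **Inputs from the protocol.** There are 3 Trusts, 4 wards per Trust, and 2 wards per arm within Trust. About 100 patients are expected at follow-up, so 100/12 = 8.3 per ward. The only sample-size figure that can be re-derived is HCA recruitment: 12 wards × 10 HCAs × 0.70 = 84, or 42 per arm. This matches the protocol and gives 7 HCAs per ward. No ICC, SD or variance component is stated.

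**Assumed.** Within-Trust ward variance σ²w = 0.05 and residual σ²e = 0.95. Between-Trust variance σ²T = 0, 0.02, 0.05 or 0.10.

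**Step 1: expected ward variance.** The sum of squares for Trust among ward means has a Trust contribution of 4 wards × 2 df × σ²T = 8σ²T. With intervention alone fitted, the ward means leave 12 − 2 = 10 df, so the residual gains 8σ²T/10 = 0.8σ²T. The between-ward variance then has expectation σ²w + 0.8σ²T. With Trust also fitted (8 df), it is σ²w.

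**Step 2: standard error.** The true variance of the arm difference is (σ²w + σ²e/m)(1/6 + 1/6) = V/3, with V = 0.05 + 0.95/8.33 = 0.164. The model without Trust uses V + 0.8σ²T instead. The SE ratio is √[(0.164 + 0.8σ²T)/0.164].

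**Step 3: net interval width.** The 97.5% t value is 2.228 on 10 df and 2.306 on 8 df. The width ratio, without Trust to with Trust, is the SE ratio × 2.228/2.306 = SE ratio × 0.966.

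**Step 4: ICC without Trust.** (0.05 + 0.8σ²T)/(0.05 + 0.8σ²T + 0.95). With Trust fitted it is 0.050.

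| σ²T | Ward variance, no Trust | ICC, no Trust | SE ratio | CI width ratio |
|---|---|---|---|---|
| 0 | 0.050 | 0.050 | 1.00 | 0.97 |
| 0.02 | 0.066 | 0.065 | 1.05 | 1.01 |
| 0.05 | 0.090 | 0.087 | 1.12 | 1.08 |
| 0.10 | 0.130 | 0.120 | 1.22 | 1.18 |

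**Break-even.** The unadjusted interval is the wider one only when σ²T exceeds [(2.306/2.228)² − 1]/0.8 = 0.089 of V, which is 0.089 × 0.164 = 0.015.

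**HCA models.** With m = 7, V = 0.05 + 0.95/7 = 0.186. The SE ratios for the same σ²T values are 1.00 / 1.04 / 1.10 / 1.20.

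**Simulation.** There were 200,000 runs per setting, with 8 patients per ward, total variance 1 and t intervals on ward means.

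- Ward share 0.05, Trust share 0.05: the mean ward variance was 0.090 without Trust and 0.050 with it. The root-mean-square SE without Trust was 0.260 against a true 0.232. Coverage was 96.6% without Trust and 95.0% with it.
- Trust share 0.10: coverage without Trust was 97.4%.
- Trust share 0: ward variance 0.050 and coverage 95.0% either way.

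**The case against.** **The inflation is conditional.** A reader might infer that the ICC and intervals from these models will be too large. The documents do not support that, because they give no between-Trust variance. At zero there is no bias, and the interval without Trust is about 3% narrower. This stands.

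**The SE figures overstate the effect on intervals.** Intervals are what the protocol reports, and fitting Trust costs degrees of freedom. After that cost the widening is 1 / 8 / 18%, not 5 / 12 / 22%. This stands.

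**The larger ICC is not wrong for every design.** A reader might infer that the definitive trial will be oversized by a set amount. That needs a trial stratified by and adjusted for Trust, and an assumed number of patients per ward. The protocol fixes neither, and it lists whether the ward is the right unit of randomisation as an open question. For an unstratified, unadjusted trial, a variance that includes Trust would be relevant. This stands as a limit on the claim.

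**Noise is large.** On the assumed inputs with σ²T = 0, the sampling SD of the ward-variance estimate is about √[(2/10)(0.164)² + (2/88)(0.114)²] = 0.075. The biases are 0.016 / 0.040 / 0.080, so two of the three are well below one SD. That limits how much a single estimate would visibly change. It does not justify an avoidable bias of known direction.

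**The consequence for inference is mild.** The 2:2 split keeps the arm estimate unbiased, and the error is conservative in an unpowered pilot. This stands.

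**The text may leave room.** The patient section's optional covariate adjustment could be read to cover Trust. It is conditional and does not name Trust, and the HCA section has nothing equivalent. This is only a partial answer.

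**Conclusion.** The inconsistency is real. Trust is in the QUIS model because it is a stratification variable, and it is missing from the stated PEECH, TEQ and AGED models. If Trusts differ, the between-ward variance is inflated by about 0.8 times the between-Trust variance. The ICC is then too large as a within-Trust planning value, and the arm-effect intervals are conservative.

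The size depends on variance components that the documents do not give. On the assumptions above it runs from nothing (σ²T = 0) to an ICC of 0.120 instead of 0.050 and an interval 18% wider (σ²T = 0.10). The point does not threaten the validity of the arm comparison. It should be corrected before analysis because the variance components are a main product of the pilot and the correction is cheap, but it is not a critical fault.

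**What to change.** Add NHS Trust (3 levels) as a fixed effect to the PEECH total and subscale models, to the TEQ and AGED models, and to the ward-mean analyses. Add it to the GEE comparison as well, with the usual caution: robust errors are already weak with 12 clusters, and two further cluster-level parameters do not help.

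Report the between-ward variance and ICC conditional on Trust as the planning values for a Trust-stratified, Trust-adjusted trial. Report between-Trust variation separately, noting that three Trusts (2 df) estimate it very imprecisely. A later team can then combine the components for whichever design is chosen.

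This needs a sentence of analysis wording and a line of reporting, with no new data. It spends two ward-level degrees of freedom (10 to 8), which makes intervals about 2.306/2.228 − 1 = 3.5% wider if Trusts do not differ.

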### Qualitative analysis

The qualitative interview data will be analysed thematically. As the purpose of these interviews is to inform the understanding of the process of both the trial and the delivery and receipt of the intervention, we will use framework analysis [40]. This is a method that is particularly useful for applied research designed to meet specific information needs yet remains true to the accounts of the interviewees.

### Ethical approval

A favourable ethical opinion for this study (CHAT (feasibility randomised controlled trial) Protocol v2 9.2.2015) was granted by Cambridge South Research Ethics Committee on 13 February 2015 (application number 15/EE/0025, CSP reference162616). Full NHS Research and Development approvals were granted for each study site (King’s College Hospital NHS Foundation Trust 17 March 2015; Norfolk and Norwich University Hospitals NHS Foundation Trust, 19 March 2015; Nottingham University Hospitals NHS Trust, 15 April 2015). The study has been adopted onto the UK CRN portfolio (study ID UKCRN18280).

## Discussion

We have made the following modification to the trial. Our ward observational tool is now the QUIS rather than the Care Kindness and Compassion Observation Tool [41] as originally specified (ISRCTN10385799). Wider use of the QUIS in research settings including another existing NIHR funded study of compassionate care in hospital wards [42] informed this decision. This change has been agreed by the study sponsor, funder and has received ethics committee approval.

## Trial status

To date, 12 wards have been enrolled into the study, 112 HCAs have consented to take part and 115 patients have consented to receive questionnaires.

## Abbreviations

AGED: Age Group Evaluation and Description
AWES: Assessment of Work Environment Schedule
CHAT: Can Healthcare Assistants Training improve the relational care of older people?
CQC: Care Quality Commission
EQ-5D-5L: European Quality of Life 5 Dimensions 5 Levels
GEE: generalised estimating equation
HCAs: healthcare assistants
NHS: National Health Service
NIHR HS&DR: National Institute of Health Research Service and Delivery Research
PEECH: Patient Evolution of Emotional Care during Hospitalisation
QUIS: Quality of Interaction Schedule
TEQ: Toronto Empathy Questionnaire
TSC: Trial Steering Committee
